**4 Follow-up**

**4.1 Timeframe**

Tumor response using contrast-enhanced computed tomography or magnetic resonance imaging should be performed every 6 weeks. Physical examination and hematological tests (complete blood count, liver function, biochemical tests) should be perform each week during radiotherapy, then every 3 weeks since the initiation of camrelizumab.

During each follow-up, patients are allowed to arrange their visits flexibly in a predefined 7-day timeframe. For example, a patient is required to visit on day 10, he or she is free to make the visit between day 7 and day 13.

Each patient should insist on a predefined specific type of imaging during follow-up. For patients contraindicated for MRI imaging due to metal implants or other reasons, CT should be performed continuously during each follow-up.

**4.2 Contents**

Following disorders should be recorded during each follow-up to evaluate the safety of different treatment plans:

- Blood and lymphatic system disorders
- Cardiac disorders
- Ear and labyrinth disorders
- Endocrine disorders
- Eye disorders
- Gastrointestinal disorders
- General disorders and administration site conditions
- Hepatobiliary disorders
- Immune system disorders
- Infections and infestations
- Injury, poisoning, and procedural complications
- Metabolism and nutrition disorders
- Musculoskeletal and connective tissue disorders
- Neoplasms benign, malignant, and unspecified (including cysts and polyps)
- Nervous system disorders
- Psychiatric disorders
- Renal and urinary disorders
- Reproductive system and breast disorders
- Respiratory, thoracic, and mediastinal disorders
- Skin and subcutaneous tissue disorders
- Vascular disorders

**5. Study population**

**5.1 Number of patients**

A total of 36 patients will be recruited in the trial. Patients withdrawn from the trial will not be replaced.

**5.2 Inclusion criteria**

1. Age: 18-75 years;
2. Histopathologically confirmed unresectable primary or postoperative recurrent intrahepatic cholangiocarcinoma without distant metastasis (Appendix 1);
3. No previous radiotherapy or systemic therapy;
4. Adequate volume of the uninvolved liver (larger than 700 mL);
5. At least one measurable lesion based on RECIST 1.1 criteria (Appendix 2);
6. ECOG PS 0-1 (Appendix 3);
7. Adequate hematologic, hepatic and renal function: ANC ≥ 1.5x10^9/L, Hb ≥ 90g/L, PLT ≥ 100 x10^9/L, albumin ≥ 28g/L, total bilirubin < 1.5×ULN at diagnosis or after biliary drainage, ALT and AST < 5×ULN, BUN and CREA<1.5×ULN, creatinine clearance rate ≥ 45ml/min;
8. Life expectancy of at least 12 weeks.

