**6. Screening and consent**

**6.1 Screening**

Potential patients will be identified via clinic referrals.

Investigators will be expected to maintain a Screening Log of all potential study candidates. This Log will include limited information about the potential candidate (e.g. date of birth and gender), the date and outcome of the screening process (e.g. enrolled into study, reason for ineligibility, or refused to participate).

For patients who appear to meet the criteria for participation in the study, the Investigator will provide patient information sheet to allow them to make an informed decision regarding their participation. If informed consent is given, the investigator will conduct a full screening evaluation to ensure that the patient satisfies all inclusion and exclusion criteria. A patient who gives written informed consent and who satisfies all the inclusion and exclusion criteria may be recruited into the study. Note that assessments conducted as standard of care do not require informed consent and may be provided as screening data.

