**7. Trial entry**

After screening and consent, patient will be registered into the trial. It is recommended that patients commence trial treatment as soon as possible after recruitment, and ideally within 2 weeks. Delays in initiation of treatment longer than this will need to be documented and approved by the CORRECT Trial Office. If a patient discontinues participation in the trial, then their trial number cannot be re-used.

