**Appendix 1 – Diagnosis**

Diagnosis of intrahepatic cholangiocarcinoma is confirmed by biopsy.

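### The bilirubin limit in inclusion criterion 7 is tied to diagnosis or to a past drainage, so as written it can be met by a patient who is above the limit at screening

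*Protocol*

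**What the plan says.** Section 5.2, criterion 7, lists the blood, liver and kidney values required for adequate organ function. For bilirubin it reads "total bilirubin < 1.5×ULN at diagnosis or after biliary drainage", and the Synopsis repeats this word for word. Bilirubin is the only laboratory value in the list with a time point of its own.

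Other provisions that bear on the timing:

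- **Population (5.2, criterion 2):** "unresectable primary or postoperative recurrent intrahepatic cholangiocarcinoma without distant metastasis".
- **Diagnosis (Appendix 1):** "Diagnosis of intrahepatic cholangiocarcinoma is confirmed by biopsy". No maximum interval from biopsy to entry is given.
- **Screening (6.1):** after consent, "the investigator will conduct a full screening evaluation to ensure that the patient satisfies all inclusion and exclusion criteria". The same section notes that "assessments conducted as standard of care do not require informed consent and may be provided as screening data".
- **Trial entry (7):** "It is recommended that patients commence trial treatment as soon as possible after recruitment, and ideally within 2 weeks". For longer intervals, "Delays in initiation of treatment longer than this will need to be documented and approved by the CORRECT Trial Office".
- **Monitoring (4.1):** physical examination and blood tests, including liver function, "should be perform each week during radiotherapy, then every 3 weeks since the initiation of camrelizumab".

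**The concern.** An entry limit on bilirubin is there to show that the liver can tolerate the treatment about to start. That calls for a value that describes the patient at entry. The criterion accepts a value from diagnosis, or from some point after a drainage, and the two are alternatives. A later rise does not undo either one.

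Two things are at stake. The first is safety: a site that follows the text could enter a patient with current biliary obstruction or hepatic impairment into liver radiotherapy followed by camrelizumab. The second is interpretation: if bilirubin is already raised when treatment starts, an early hepatic adverse event is harder to attribute to the regimen. Biliary obstruction is foreseen in this population, since Section 8.4 allows drainage during the study, although the protocol gives no frequency for it.

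**Working it through.** No arithmetic applies. The check is whether the criterion as worded requires an acceptable bilirubin at entry and, if not, whether another provision does.

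**Step 1: the logic of the criterion.** A patient meets the bilirubin part if

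(value at diagnosis < 1.5×ULN) OR (value after drainage < 1.5×ULN).

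The value at screening appears in neither term. Two patients, both above the limit at screening:

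| Patient | History | Bilirubin part as written |
| --- | --- | --- |
| A | Below the limit at diagnosis, risen since, not drained | Met by the first term |
| B | Drained earlier, one value below the limit afterwards, risen since | Met by the second term |

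**Step 2: how far back the qualifying value may lie.** Appendix 1 ties diagnosis to biopsy and sets no maximum interval to entry. Criterion 2 admits postoperative recurrence. For such a patient the word diagnosis could mean the original disease or the recurrence, and the protocol does not say which. The second term does not ask for the most recent value after drainage.

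**Step 3: does any other provision restore a limit at entry?**

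| Provision | What it does | Restores a bilirubin limit at entry? |
| --- | --- | --- |
| 6.1, full screening evaluation | Checks the patient against the criteria as worded, so it carries the same timing with it | No |
| 6.1, standard-of-care results | May serve as screening data; silent on their age | No |
| 7, trial entry | Two weeks to treatment is a target; longer delays need documentation and approval | No |
| 5.3, exclusion criteria | None names bilirubin, jaundice or biliary obstruction; item 12 on other comorbidities is left to judgement | No |
| 5.2, rest of criterion 7 | Albumin, ALT and AST limits apply, but they are different tests | No |
| 4.1, weekly tests in radiotherapy | Monitoring once treatment has begun | No |
| 8.4, concomitant therapy | Allows drainage on study | No |

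**Step 4: can the protocol tie a value to entry when it means to?** Yes. Exclusion 7 sets its QTc limit at screening, and exclusion 5 counts antiplatelet use back from enrolment. The bilirubin criterion names a date too, but not one linked to entry. It is therefore a stated time point that is badly placed, not a detail left for another document.

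**The case against.** The best defence is that the reading is too literal. The phrase most naturally describes two kinds of patient: those within the limit without drainage, and those within it once drained. The heading of the criterion asks for adequate hepatic function, and an investigator doing a full screening evaluation would probably look at a current bilirubin. The other liver tests, ECOG 0-1, a life expectancy of at least 12 weeks, the exclusion of perihilar and distal tumours, and the open comorbidity exclusion all narrow who could slip through. This stands as an account of the likely intent and of why the number affected may be small. It does not change what the words permit, and none of these safeguards sets a bilirubin limit at entry.

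Four stronger readings are tempting, and the protocol does not support them:

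- **That Section 6.1 accepts results of any age.** It is silent on age. Silence leaves the gap open but is not permission.
- **That the qualifying value may be months or years old.** This needs diagnosis to mean the pre-surgical diagnosis in a recurrent patient. The recurrence is an equally possible reading.
- **That hepatic adverse events become uninterpretable.** Section 10.1 requires a Baseline Assessment Form before treatment and an Adverse Event Monitoring Form at baseline. Section 9.1.1 counts abnormal laboratory findings as adverse events, Section 9.1.3 collects events from trial entry, and liver function is tested weekly during radiotherapy. Attribution is harder, not impossible.
- **That each such patient costs the regimen 1/36 = 2.8 percentage points of 1-year PFS.** That is one patient's share if all 36 are analysed, and it says nothing about how many are affected. Section 13.2 limits both the efficacy and the safety population to patients given at least one dose of camrelizumab, so a patient who stops during radiotherapy is in neither. Biliary obstruction is also not itself a PFS event under Section 2.2.

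**Conclusion.** The point holds as a fault in the eligibility wording. As written, the bilirubin part of criterion 7 can be met by a patient whose bilirubin is above the limit at screening, which works against the criterion's own purpose, and no other provision corrects it. This rests on the literal text only. It does not show that such patients were or would be enrolled, and the intent was probably a current value.

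The consequence is a possible safety risk and harder attribution of early hepatic events. The number of affected patients is unknown. Neither the size nor the direction of any effect on 1-year PFS can be derived from the protocol, and the sample size of 36 is not touched. The point is worth correcting because the remedy is specific and cheap and bears on patient safety.

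**What to change.** In Section 5.2, criterion 7, and in the Synopsis, replace the present timing of the bilirubin value with the screening evaluation. Where drainage was needed, specify the most recent value after it. Leave the numerical threshold as it is.

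Then reconcile the new wording with Sections 6.1 and 7. The sponsor should decide and state how old a result may be when it is used as screening data, and how the bilirubin criterion is handled when treatment starts later than the two-week target. This review does not propose a window, or a retest condition before a delayed start; both are the sponsor's decisions.

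The cost is a short change in two places plus the reconciliation. In practice it may mean a few repeat blood tests or screen failures.

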**5.3 Exclusion criteria**

1. Have acute or chronic active hepatitis B or C, HBV-DNA＞2000IU/ml or 10^4^ copy/ml; HCV-RNA＞10^3^ copy/ml; both HBsAg and HCV antibody are positive. If the related results become lower than above standards after anti-viral treatment, the patients are qualified for enrollment;
2. Have distal or perihilar cholangiocarcinoma, gallbladder cancer or carcinoma of the ampulla of Vater; have metastasis in extrahepatic distant organs including lung, central nervous system, bone etc., or extrahepatic lymph node metastasis beyond abdomen;
3. Have risky bleeding events requiring transfusion, operation or local therapies, continuous medication in the past 3 months;
4. Have thromboembolism in the past 6 months, including myocardial infarction, unstable angina, stroke or transient ischemic attack, pulmonary embolism, deep vein thrombosis;
5. Have taken aspirin (＞325mg/day) or other antiplatelet drugs continuously for 10 days or more within 2 weeks before enrolment;
6. Uncontrollable hypertension, systolic pressure＞140mmHg or diastolic pressure＞90mmHg after best medical care, or history of hypertensive crisis or hypertensive encephalopathy;
7. Symptomatic congestive heart failure (NYHA class II-IV). Symptomatic or badly-controlled arrhythmia. Congenital long QT syndrome or modified QTc＞500ms upon screening;
8. Have active autoimmune diseases that require systemic treatment within 2 years before enrolment;
9. Active tuberculosis, having antituberculosis therapy at present or within 1 year;
10. Have a known history of prior invasive malignancies within 5 years before enrolment;
11. Pregnant or breastfeeding women, or expecting to conceive or father children within the projected duration of the trial;
12. Have other uncontrollable comorbidities;
13. Infection of HIV, known syphilis requiring treatment;
14. Allergic to elements of camrelizumab.

**6. Screening and consent**

**6.1 Screening**

Potential patients will be identified via clinic referrals.

Investigators will be expected to maintain a Screening Log of all potential study candidates. This Log will include limited information about the potential candidate (e.g. date of birth and gender), the date and outcome of the screening process (e.g. enrolled into study, reason for ineligibility, or refused to participate).

For patients who appear to meet the criteria for participation in the study, the Investigator will provide patient information sheet to allow them to make an informed decision regarding their participation. If informed consent is given, the investigator will conduct a full screening evaluation to ensure that the patient satisfies all inclusion and exclusion criteria. A patient who gives written informed consent and who satisfies all the inclusion and exclusion criteria may be recruited into the study. Note that assessments conducted as standard of care do not require informed consent and may be provided as screening data.

**6.2 Informed consent**

Patients will be required to give informed consent at registration. It is the responsibility of the investigator (research nurses) to obtain written informed consent for each patient prior to entering the trial or, where relevant, prior to evaluating the patient’s suitability for the study.

The Patient Information Sheet is provided to facilitate this process. Investigators must ensure that they adequately explain the aim, trial treatment, anticipated benefits and potential hazards of taking part in the trial to the patient. The investigator should also stress that the patient is completely free to refuse to take part or withdraw from the trial at any time. The patient should be given ample time (e.g. 24 hours) to read the Patient Information Sheet and to discuss their participation with others outside of the site research team. The patient must be given an opportunity to ask questions which should be answered to their satisfaction. The right of the patient to refuse to participate in the trial without giving a reason must be respected.

If the patient expresses an interest in participating in the trial they should be asked to sign and date the latest version of the Informed Consent Form. The investigator or designate must then sign and date the form. A copy of the Informed Consent Form should be given to the patient, a copy should be filed in the hospital notes, and the original placed in the Investigator Site File (ISF). Once the patient is entered into the trial the patient’s trial number should be entered on the Informed Consent Form maintained in the ISF. In addition, if the patient has given explicit consent, a copy of the signed Informed Consent Form must be sent in the post to the Trials Office for review.

Details of the informed consent discussions should be recorded in the patient’s medical notes, this should include date of, and information regarding, the initial discussion, the date consent was given, with the name of the trial and the version number of the Patient Information Sheet and Informed Consent Form. Throughout the trial the patient should have the opportunity to ask questions about the trial and any new information that may be relevant to the patient’s continued participation should be shared with them in a timely manner. On occasion it may be necessary to re-consent the patient in which case the process above should be followed and the patient’s right to withdraw from the trial respected.

Electronic copies of the Patient Information Sheet and Informed Consent Form are available from the Trials Office and should be printed or photocopied onto the headed paper of the local institution.

Details of all patients approached about the trial should be recorded on the Patient Screening/ Enrolment Log.

**7. Trial entry**

After screening and consent, patient will be registered into the trial. It is recommended that patients commence trial treatment as soon as possible after recruitment, and ideally within 2 weeks. Delays in initiation of treatment longer than this will need to be documented and approved by the CORRECT Trial Office. If a patient discontinues participation in the trial, then their trial number cannot be re-used.

**8. Treatment details**

**8.1 Treatment**

The total radiation dose is over 45Gy without damaging organic function. Conventional intensity-modulated radiotherapy or stereotactic body radiation therapy are both allowed. Camrelizumab 200mg intravenously every 3 weeks will be initiated within 7 days after radiotherapy. Patients will receive camrelizumab until clinical or radiographic disease progression, unacceptable toxicity, death or withdrawal. Considering the possibility of pseudoprogression, patients with initial judgment of disease progression were treated with an additional 200 mg of camrelizumab, and radiologic examination was performed 4 weeks later to confirm whether it was pseudoprogression or disease progression. If progression is confirmed, the camrelizumab should be stopped.

**8.2 Treatment discontinuation**

In the event of discontinuation of trial treatment, full details of the reason(s) for discontinuation should be recorded in the patient’s medical notes and on the appropriate pages on the Case Report Form (CRF). All patients, including non-compliant subjects, should be followed up according to the protocol unless they withdraw consent.

A patient should discontinue the trial drug in the event of any of the following:

• Disease Progression (Radiological disease progression, Clinical disease progression

• Unacceptable toxicity

• Any other adverse event which, in the Investigator’s opinion, requires termination of the trial medication

• Administration of any other anti-tumor therapies during the trial

• Pregnancy

• Any other reason given by the Investigator

• The patient uses illicit drugs or other substances that may, in the opinion of the Investigator, have a reasonable chance of contributing to toxicity or otherwise interfering with results

• The development of a second malignancy that requires treatment

• Request by the patient or a legal representative/relative to stop the treatment

• Death or End of Trial

**8.3 Patient withdrawal**

Participants are free to withdraw from the study at any stage and may be withdrawn by the Investigator at any stage.

The following are justifiable reasons for the Investigator to withdraw a patient from study:

• Unacceptable toxicity

• Unforeseen events: any event which in the judgement of the Investigator makes further treatment inadvisable

• Serious Adverse Event (SAE) requiring discontinuation of treatment

• Serious violation of the study protocol (including persistent patient attendance failure and persistent non-compliance)

• Withdrawal by the Investigator for clinical reasons not related to the study drug treatment

Participant withdrawals will not be replaced. If withdrawal is decided for a patient, we will provide a withdrawal of consent for him/her to choose to withdraw but still provide follow-up data, withdraw but allow data up to the withdrawal day to be used for analysis or withdraw and remove all trial data.

The details of withdrawal should be clearly documented in the patient’s hospital notes and communicated to the Trial Office on a Withdrawal Form.

The following should be clearly documented in the medical notes:

The date and reason the patient withdraws consent. If no reason for withdrawal is specified by the patient concerned this will also need to be documented in the medical notes. The patient should not be pressured in any way to give a reason for withdrawal if he/she does not wish to supply this information.

We will provide counseling service of other therapeutic approaches for patients withdrawing from the study.

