**2.2 Primary endpoint**

**1-year progression-free survival (PFS) rate**: defined as the rate of patients free of progressive disease at one year according to RECIST 1.1. Progression-free survival (PFS) was defined as the time from the commencement of radiotherapy until disease progression or death from any cause, whichever happens first. Patients who withdraw or who are lost to follow-up will be censored at the date of the last adequate tumor assessment. Patients not having an event will be censored at the date of the last adequate tumor assessment. If patients don’t have baseline tumor assessments, they will be censored at the date of the first treatment.

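### Sections 8.2, 8.3 and 2.2 do not agree on whether a patient taken off study by the investigator is still followed, and 8.3 allows removal of all data with no safety exception

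*Protocol*

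**What the plan says.** Section 8.2 (Treatment discontinuation) lists reasons to stop the trial drug, among them toxicity and other adverse events. On follow-up it is unconditional apart from consent: "All patients, including non-compliant subjects, should be followed up according to the protocol unless they withdraw consent".

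Section 8.3 (Patient withdrawal) concerns leaving the study: "Participants are free to withdraw from the study at any stage and may be withdrawn by the Investigator at any stage". Its list of reasons is headed "The following are justifiable reasons for the Investigator to withdraw a patient from study". The list includes unacceptable toxicity, "Serious Adverse Event (SAE) requiring discontinuation of treatment", and serious protocol violation, which is said to cover persistent non-attendance and non-compliance.

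Once a withdrawal is decided, 8.3 provides a withdrawal-of-consent form with three choices. The first is "for him/her to choose to withdraw but still provide follow-up data". The second allows use of data up to the day of withdrawal. The third is "or withdraw and remove all trial data". Withdrawn patients are not replaced.

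Section 2.2 (Primary endpoint) sets the PFS rule: "Patients who withdraw or who are lost to follow-up will be censored at the date of the last adequate tumor assessment". Section 2.3 censors overall survival (OS) for withdrawn patients at the date last known alive. Section 3 (Design) also names patient withdrawal as an end of follow-up.

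**The concern.** The same event, such as a toxicity that stops the drug, leads to continued follow-up under 8.2 and to permitted exit from the study under 8.3. A site cannot tell which rule governs. If it follows 8.3, section 2.2 censors the patient at the last scan.

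Kaplan-Meier estimation assumes that a censored patient has the same outlook as those still at risk. A patient removed for toxicity, an SAE or failure to attend plausibly has a worse one. Censoring such patients would then push the 1-year PFS estimate up. The trial is open-label, single-arm and planned for 36 patients without replacement, so a few patients carry weight.

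Removal of all data raises a second problem. Section 9.1.1 requires all adverse events (AEs) to be reported. Section 9.2.1.3 requires follow-up of SAEs until resolution or stabilization. Section 13.3 promises summaries of SAEs and of AEs that led to stopping treatment. Those are the kinds of event for which 8.3 permits withdrawal. An analysis plan cannot recover scans that were never taken or data that were removed.

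**Working it through.** **The passages side by side**

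| Situation | 8.2 | 8.3 | 2.2 (PFS) |
|---|---|---|---|
| Toxicity or an adverse event stops the drug | Follow-up continues | Investigator may withdraw from study | Censored if withdrawn |
| Non-compliance | Follow-up continues | Investigator may withdraw from study if persistent | Censored if withdrawn |
| Withdrawn, agrees to further follow-up | Follow-up continues | Offered as first choice | Still censored as worded |
| Withdrawn, asks for removal of data | Not addressed | Offered as third choice, no safety exception | No record left |

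**The plan's own sample size.** Inputs from section 13.6: null 1-year PFS 20%, alternative 40%, two-sided 5%, power 80%, 10% loss or non-adherence. The protocol does not name its formula. A normal approximation with the null variance gives

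n = (1.960 + 0.842)² × 0.2 × 0.8 / 0.2² = 31.4, rounded up to 32; 32 / 0.9 = 35.6, rounded up to 36.

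This reproduces the stated 36. The point made here does not depend on N.

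**Illustration of the effect.** Assumptions, none of them in the protocol: all 36 are in the efficacy set; 3 or 4 patients (about 10% of 36) are withdrawn; all of them would have failed by 1 year; they are deleted, or censored before the first event, so that Kaplan-Meier reduces to a simple proportion. The exact test uses P(X ≥ x) for a binomial with rate 0.20, against 0.025 (half of the two-sided 5%). The normal test uses z = (x/n − 0.2) / √(0.16/n), against 1.96.

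| Event-free / n | Rate | Exact 95% CI | Exact p | z |
|---|---|---|---|---|
| 12/36 (all followed) | 33.3% | 18.6 to 51.0 | 0.042 | 2.00 |
| 12/34 | 35.3% | 19.7 to 53.5 | 0.027 | 2.23 |
| 12/33 | 36.4% | 20.4 to 54.9 | 0.022 | 2.35 |
| 12/32 | 37.5% | 21.1 to 56.3 | 0.017 | 2.47 |
| 13/36 (all followed) | 36.1% | 20.8 to 53.8 | 0.018 | 2.42 |
| 11/36 (all followed) | 30.6% | 16.4 to 48.1 | 0.089 | 1.58 |
| 11/32 | 34.4% | 18.6 to 53.2 | 0.041 | 2.03 |

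Under the exact test with everyone followed, 13 of 36 are needed to reject 20%. Losing 3 or 4 failures lets 12 suffice; losing 2 does not. Under the assumption that 3 or 4 failures are always lost, the true type I error is P(X ≥ 12 of 36) = 0.042 instead of P(X ≥ 13 of 36) = 0.018.

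Under the normal test, 12/36 already rejects (z = 2.00). The count at which 4 lost failures change the decision is then 11 (1.58 to 2.03).

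At a true rate of 20%, losing 4 failures gives an apparent rate of 0.20 × 36 / 32 = 22.5%.

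**The case against.** **The conflict may be loose wording.** Section 8.3 follows a decided withdrawal with a form on which the patient chooses, and the first choice keeps follow-up. Follow-up would then end only if the patient wishes, which is what 8.2 requires. Two of the five reasons in 8.3 are also phrased as treatment decisions. This softens the conflict but does not remove it: the list is headed as withdrawal from the study, and 2.2 censors anyone who withdraws without exempting those who agreed to continue.

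**Deletion is not the investigator's act.** A reader might infer that an investigator can remove a patient and erase the record. The text does not support that. Erasure is the patient's choice, one of three, and nothing suggests that it would be common.

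**The numbers are fragile.** The 10% in 13.6 covers loss to follow-up and non-adherence, not withdrawal for toxicity. That the withdrawn patients are failures is an inference. With 4 lost, the exact decision changes only at 12 event-free: 11/32 does not reject, and 13/36 rejects with everyone followed. The protocol names no test, and under the normal approximation that gives 36 the change falls at 11. All of this stands. The calculation shows sensitivity and does not predict a false positive result.

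**Serious toxicity is reported by other routes.** SAEs go to the Trials Office and to the manufacturer within 24 hours (9.2.1.2, 9.2.6). The data monitoring committee reviews them (9.2.5), serious adverse reactions go to the ethics committee (9.2.3), and source records are kept at least 5 years (10.2). A reader might infer that toxicity could vanish unseen; for serious events these routes speak against it. What stands is narrower: the final AE tables could lose patients, and 8.3 is not reconciled with these duties.

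**Conclusion.** The point holds as a conflict between sections 8.2, 8.3 and 2.2, plus a data-removal option that is not reconciled with the safety reporting and summaries in 9.1.1, 9.2.1.3 and 13.3. Applied as written, the rules allow censoring that may be informative, and the likely direction is an upward bias in 1-year PFS.

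The size is not known from the protocol. If 3 or 4 of 36 patients were lost and all were failures, the estimate at 12 event-free would rise from 33.3% to 36.4% or 37.5%, about 3 to 4 percentage points. That can decide the test, but only at particular counts and depending on the test used. A reader might infer that the rules will produce a spurious positive result, or that withdrawn patients are known failures; the documents support neither. Confidence is high on the textual conflict and low on its size. The change should be made because it is cheap and because follow-up that has lapsed cannot be restored at analysis.

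**What to change.** 1. Reconcile 8.2 and 8.3 so that stopping treatment and leaving the study are separate, and only withdrawal of consent ends follow-up. Bring the follow-up statement in section 3 into line. Which reasons should stop treatment is left to the sponsor.
2. State in 2.2, and likewise for OS in 2.3, that patients who stop treatment, or who withdraw but agree to further follow-up, remain in PFS and OS follow-up and are not censored at withdrawal.
3. State in 8.3 that data collected up to withdrawal are kept, at minimum the safety data, as far as the applicable data-protection law allows. Section 16 ties data handling to a law that is not among the documents, so whether full removal can be dropped must be checked by the sponsor.

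The cost is revised wording in the protocol and consent form, and a narrower data-removal choice for patients. The sample size does not change.
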